**Sample size**

Based on data from the Australian Bureau of Statistics, we anticipate approximately 89 Aboriginal youth turning 15 years old each month in Perth over the study period.
^
32
^ Using the primary outcome definition, monthly numbers of young people before their 15
^th^ birthday fully vaccinated against HPV, will be the unit of aggregation in the regression models. A total of 72 monthly data points (2020-2025) will provide 85% power to detect a one-standard-deviation shift in the average proportions post-intervention, at an α = 0.05 and a first-order autoregressive model with autocorrelation of 0.3.
^
38
^ Empirical research has shown autocorrelations of the order of 0.3 (median 0.33; IQR 0.03, 0.58; 36 ITS studies in public health).
^
39
^

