**Data analysis**

*Interrupted time series*

A linear, segmented interrupted time series analysis will be used to evaluate the impact of the social media programme on HPV vaccination.

For the primary outcome, we will count the number of youths aged between 12 and before their 15
^th^ birthday who have received the HPV vaccination per month. Similarly, for the secondary outcome, we will count the number of young people aged up to 25 (inclusive) who have received the HVP vaccination per month. Our analysis models will include two segments: a pre-interruption period of 49 months, beginning on Jan 2020-Dec 2023, and a post-interruption period of 24 months, beginning on Jan 2024-Dec 2025, which encompasses both the intervention and post-intervention periods.

For each outcome, we will fit the following statistical model (Model 1), separately for the intervention and control series:

$$\text{Model}\;1:\log Y_{t}=\beta_{0}+\beta_{1}t+\beta_{2}I+\beta_{3}\left(t-T_{I}\right)I+\text{seasonal}+\text{offset}+\epsilon_{t}$$
where

$Y_{t}$
 is the outcome value at time t, and

$T_{I}$
 is the time of the interruption. The variable

I
 indicates the post-interruption segment, which is equal to 1 post the interruption and 0 before. Parameter

$\beta_{0}$
 is the intercept at the beginning of the series,

$\beta_{1}$
 is the slope in the first segment,

$\beta_{2}$
 is the level change between the expected value (based on the pre-interruption data) and the observed data, and

$\beta_{3}$
 is the difference in slope compared to

$\beta_{1}$
. The error term,

$\varepsilon_{t}$
 represents deviations from the fitted model, and we will assume these to have lag-1 autocorrelation. Seasonality will be accounted for by including two pairs of sine and cosine harmonics with periods of 12 and 6 months.
^
40,
41
^ Due to the changing of the vaccine schedule in the year following the interruption, the seasonal components will be phase shifted by six months for that year. The log of the relevant population (i.e. all Aboriginal youth aged between 12 and before their 15
^th^ birthday per month) will be included as an exposure offset to adjust for any changes to the population over time. We will assume a negative binomial distribution with a log link function. We will fit these models using the glarma package in R.
^
42
^

The effect measures of interest will be:

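### Large-sample tests from the Model 1 fit would reject about 9–13% of the time at a nominal 5%, and more if autocorrelation is high

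*Protocol article*

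**What the plan says.** The Data analysis section fixes Model 1 closely. It has four segmented-regression coefficients (β0 to β3), two sine–cosine pairs, a six-month phase shift of the seasonal terms in the year after the interruption, and a population offset. On the errors: "we will assume these to have lag-1 autocorrelation". On the distribution: "We will assume a negative binomial distribution with a log link function". The software is the glarma package. The two effect measures are the level change three months after the campaign begins and the change in slope. The planned graphs carry confidence intervals.

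The error rate appears only under Sample size: "A total of 72 monthly data points (2020-2025) will provide 85% power" for a shift of one standard deviation, "at an α = 0.05 and a first-order autoregressive model with autocorrelation of 0.3". That section also gives the spread of autocorrelation in earlier interrupted time series: "median 0.33; IQR 0.03, 0.58; 36 ITS studies in public health".

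The article does not say which test or interval method will be used, and it mentions no small-sample correction.

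**The concern.** Model 1 estimates ten quantities from 72 points: eight mean parameters, one lag-1 coefficient and one dispersion. Only 24 of the points lie after the interruption. In a short series, the flexible mean absorbs part of the serial dependence and part of the extra-Poisson variation. Both are then underestimated, and the model's own standard errors are too small.

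If so, the 0.05 on which the power statement rests is not what ordinary output from the fit would deliver. The main question is whether the campaign raised vaccination, and the Dissemination section proposes carrying a successful model to other communities. A chance finding would then be about twice as likely as stated, and intervals would be too narrow. Model 1 is also refitted in two sex groups and five locations for both outcomes, so the same weakness may recur there.

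**Working it through.** **Inputs from the protocol.** 72 months; α = 0.05 (taken as two-sided); lag-1 autocorrelation 0.3, interquartile range 0.03 to 0.58; mean parameters 4 + 4 = 8. The segments are given as "a pre-interruption period of 49 months, beginning on Jan 2020-Dec 2023" and "a post-interruption period of 24 months, beginning on Jan 2024-Dec 2025". January 2020 to December 2023 is 48 months, and 48 + 24 = 72, so 48/24 is used.

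**Assumed inputs, not in the protocol.** Mean monthly count 70 in the main set, with 30 and 300 also tried (the protocol expects about 89 young people to turn 15 each month). Negative binomial size parameter α_NB of 5, 10 or 30 (the dispersion; variance μ + μ²/α_NB). Seasonal amplitude 0.6 on the log scale.

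**Step 1: the plan's own figure.** With a step-only mean (intercept and level shift), AR(1) errors at 0.3 and a 48/24 split, generalised least squares gives SE = 0.332 SD. Power = Φ(1/0.332 − 1.96) = Φ(1.05) = 85.4%. A 49/24 split gives 85.6%. The stated 85% therefore reproduces, but with the autocorrelation and variance treated as known and the 5% test treated as exact.

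**Step 2: simulation under no effect.** The fitted model was log μ_t = x_t′β + Z_t, with Z_t = φ(Z_{t−1} + e_{t−1}) and e_t = (Y_t − μ_t)/√(μ_t + μ_t²/α_NB). The phase shift was included and fitting was by maximum likelihood. The test was |estimate/SE| > 1.96. The main set had 1500–2000 series per scenario, so the Monte Carlo error is about √(0.12 × 0.88/1500) = 0.8 points.

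| Data generated from | Wald, level change β2 | Likelihood ratio (α_NB = 10) |
|---|---|---|
| Planned model, no autocorrelation | 11–12% | 9.9% |
| Planned model, about 0.3 | 9–11% | 8.3% |
| Planned model, about 0.5 | 9–10.5% | 7.7% |
| Latent log-AR(1), 0.3 | 12–13% | 10.6% |
| Latent log-AR(1), 0.45 | 14% | 13.5% |
| Latent log-AR(1), 0.58 | 18% | 17.1% |

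The level change at three months and the slope change behave similarly (9–13% up to 0.3). At the planned 0.3, mean counts of 30 and 300 give 10.7% and 9.9%, so the count level matters little. A t cut-off of about 2.00 recovers only 0.5–1 point.

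**Step 3: why.** At α_NB = 10 and mean 70, √(1/70 + 1/10) = 0.338, so an autocorrelation of 0.3 corresponds to φ = 0.3 × 0.338 = 0.101. The mean estimate of φ was 0.061, that is 0.061/0.338 = 0.18 instead of 0.3. The median estimate of α_NB was 12.0 against a true 10, so the fitted variance was too small. The true spread of the level estimate was 1.17 times the model SE. From this alone one expects 2Φ(−1.96/1.17) = 9.4%, in line with the table. A negative binomial fit without a lag term on independent data gave 6.6% (500 runs), so most of the excess comes from estimating the lag term alongside so many mean parameters.

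**Step 4: other simulations, separately programmed.**
- About 1000 runs (mean about 60, dispersion 10), three-month level change: 11.3% with no autocorrelation, 11.0% under the planned model near 0.3, 9.9% at latent 0.3, 17.1% at latent 0.58. Slope change in the same order: 10.1%, 9.4%, 13.1%, 22.7%.
- 400 runs (mean 60, dispersion 10), level change: 11.5%, 9.5% and 10.3% under the planned model at lag effects 0, 0.1 and 0.3; 15% and 20% at latent 0.3 and 0.58.
- 400 runs (mean 55), level change: 14.2% with no autocorrelation, 15.5% at autoregressive 0.3, 12.2% at latent 0.4. This is the highest set under the planned model; its Monte Carlo error is about 1.8 points.

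**The case against.** The strongest reply is that the article names no test, and that the choice of interval and p-value method normally belongs in an analysis plan that is not shown. It is true that Wald inference is assumed here. But the usual alternatives do not cure the problem: the likelihood-ratio test still rejects about 8–11% under the planned model or at a latent 0.3, and a t cut-off changes little. The article fixes the model and the series length, and these cause the difficulty.

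It is also fair that nobody ran glarma itself and that the rates rest on assumed count level, dispersion and seasonality. The separate implementations agree on direction in every scenario with an estimated lag term, but differ by several points in size. Only a range is defensible.

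A reader might infer more than this supports:
- **A fixed error rate of 12–16%, or two to three times nominal.** Larger runs at the protocol's own 0.3 give 9–11% when the data follow the planned model.
- **A combined error of about 20% for either effect measure.** This presumes that success on either measure suffices, and the article states no such rule.
- **The same fault in Model 2.** Only single 72-point series were simulated. The article also interprets its findings by comparing the two models, not from one Model 1 test.

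**Conclusion.** The concern holds in a limited form. Ordinary large-sample inference from the Model 1 fit is too liberal: about 9–13% instead of 5% under the planned model or at a latent autocorrelation near 0.3, with single runs up to about 15%, and about 17–23% at 0.58. The last range reads the cited upper quartile as the autocorrelation of a latent process, which the fitted lag-1 structure does not match. When the data do follow the planned model, the rate at 0.5 stays near 10%. The conclusion rests on about 55–70 events per month, dispersion of about 5–30, moderate seasonality, Wald tests and own code. Under those assumptions it is a correctable weakness in the planned inference; it does not invalidate the design or the model.

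**What to change.** State that, for Model 1, confidence intervals and p-values for the three-month level change and the slope change come from a studentised parametric bootstrap of the fitted model with at least 2000 replicates. Alternatively, refer the likelihood-ratio statistic to a null distribution simulated from the fitted null model. A fixed replacement cut-off should not be used, because the critical value depends on the autocorrelation. Run the same simulation for Model 2, in glarma, to see whether it needs the same treatment.

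The cost is computing time, a sentence of text and wider intervals. The |z| cut-off that restored 5% for the level change ran from about 2.2 (2.2/1.96 = 1.12) to about 2.93 (2.93/1.96 = 1.49), so intervals would be roughly 12–50% wider.

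The remedy is partial. In a one-resample approximation, the bootstrap brought the level and slope error to 3–5% under the planned model and 6–7% at latent 0.3, but only to 10–13% at latent 0.58. The report should therefore show residual autocorrelation and say so if the lag-1 model fits poorly.

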## Introduction

Human papillomavirus (HPV) is a common sexually transmitted infection that can lead to HPV-related cancers such as cervical cancer and other cancers such as anal, vaginal, and penile cancer.
^
1,
2
^ HPV rarely produces symptoms and cannot be cured or treated; therefore, vaccination is essential to protect against HPV and HPV-related diseases.

In 2007, Australia initiated the HPV vaccine through the National Immunisation Program (NIP) to girls aged 12 to 13 years in 2007 and to boys in 2013; catch up programs were implemented for older age groups. Up until 2023, the HPV vaccine provided as a free two-dose program for both males and females aged 12-13 years, with doses given between 5-6 months apart through school-based programs.
^
3
^ Responding to the global decline in HPV vaccination, lack of access to the vaccine and cost and burden required for two doses, WHO released updated recommendations in 2022 that a single dose was effective in reducing HPV.
^
4
^ As of 2023, Australia has transitioned to the single dose for 12-13 year olds through the NIP delivered at school with young people up to 26 years old also eligible for the free HPV vaccine. If a vaccine dose is missed at school, depending on their place of residence, a young person may receive a free catch-up dose at their school, their local Aboriginal or government health centre, or private general practitioner.

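### One seasonal pattern is fitted across 2020-2023 although the school schedule changed from two doses to one in 2023, which can bias and blur the Model 1 effect estimates if the outcome is full vaccination

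*Protocol article*

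**What the plan says.** In the protocol's Data analysis section, Models 1 and 2 share this seasonal specification: "Seasonality will be accounted for by including two pairs of sine and cosine harmonics with periods of 12 and 6 months". The baseline is "a pre-interruption period of 49 months, beginning on Jan 2020-Dec 2023" (those dates span 48 months). One departure is allowed. Because of a schedule change placed in the year after the interruption, "the seasonal components will be phase shifted by six months for that year".

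The Introduction dates a schedule change elsewhere. It describes the earlier programme as having two doses, and on their spacing it says "with doses given between 5-6 months apart through school-based programs". On the later programme it says "As of 2023, Australia has transitioned to the single dose for 12-13 year olds through the NIP delivered at school".

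The wording of the outcome varies. The Sample size section counts youths "fully vaccinated against HPV" as the unit for the regression models. The Setting section links the primary outcome to reporting of completion. The Outcomes and Data analysis sections speak only of receiving the vaccination and do not say which dose counts in the two-dose years.

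Model 1 is fitted separately to each series. The named effect measures are the level change three months after the campaign begins and the change in slope. Model 1 is also the only model for the sex and location subgroups. Model 2 adds the control series.

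**The concern.** Under a two-dose course, a youth became fully vaccinated at the second school visit. From 2023 this happens at the only visit. A count of full vaccination therefore has its peak about half a year apart in 2020-2022 and in 2023, and both periods lie in the baseline that defines the counterfactual. A single set of harmonics averages two nearly opposite shapes. The seasonality left over goes partly into the level and slope terms and partly into the residual variance. This happens even if yearly totals are flat and there is no trend. The plan already accepts that a schedule change can move the seasonal pattern enough to need modelling, but it does so for one year only, and not for 2023.

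**Working it through.** **The plan's own figure.** The protocol gives no figure on seasonality. The nearest is 85% power for a one-standard-deviation shift. A step model without trend or seasonal terms, autocorrelation 0.3 and a 48/24 split has standard error 0.332, so power = Φ(1/0.332 - 1.96) = Φ(1.05) = 85.4% (84.6% for a 49/23 split). The figure is reproduced, but it does not bear on this point.

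**Mechanism, six-month gap.** Let the 12-month term in the single-dose calendar be a·cos(2π(m-p)/12). Moving it six months reverses its sign, while the 6-month term is unchanged. In 2020-2022 (36 months) the coefficient is -a. In 2023, in 2024 (measured against the shifted regressor) and in 2025 (36 months) it is +a. One common coefficient is therefore about (36×(-a) + 36×a)/72 = 0, and the annual cycle goes largely unmodelled.
- *Direction.* With a peak between March and June, the shifted 2024 pattern has its trough where the peak used to be. The first months after the interruption lie below the fitted line, and the level change is pulled down.
- *Precision.* The unmodelled cycle adds about a²/2 to the log-scale residual variance. With an assumed 600 vaccinations a year (50 a month, Poisson part 1/50 = 0.02) and dispersion 0.03, the variance rises from 0.05 to 0.05 + 0.125 = 0.175 for a = 0.5, and to 0.55 for a = 1.0. The standard error rises by √(0.175/0.05) = 1.9 to √(0.55/0.05) = 3.3 times.

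**Fits of Model 1.** Assumptions not in the documents: log-scale amplitudes for the 12- and 6-month terms of 0.5/0.15 to 1.0/0.5, second dose 5 or 6 months after the first, peaks between March and June, and flat yearly totals. The year after the interruption is read as 2024. The fits were negative binomial with log link, without the autoregressive term, and with no campaign effect. Level ratio at three months = exp(β2 + 3β3), β3 per month. The truth is 1.00 for both measures.

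| Outcome in 2020-2022 (2024 shift true and modelled) | Level, as planned | Slope per year, as planned | Level, own harmonics from 2023 |
|---|---|---|---|
| Fully vaccinated, amplitudes 0.5/0.3 and 1.0/0.5 | 0.84-0.96 | 0.95-1.04 | 1.00 |
| Fully vaccinated, amplitudes 0.5/0.15 and 0.9/0.3 | 0.86-0.98 | not stable in sign | 1.00 |
| First dose, calendar unchanged | 1.00 | 1.00 | 1.00 |
| First dose, share at visit 2 falling from 20-30% to 10% | 0.96-0.99 | - | within 0.8% of 1.00 |

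As a rough yardstick, an assumed five-point rise from the 51% Year 7 uptake that the Introduction gives for Perth is 56/51 = 1.10.

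**Precision in simulation.** With about 800 vaccinations a year, the standard error of the log level change was 0.19-0.30 as planned and 0.09-0.10 with separate harmonics. With autocorrelated noise it was 0.39-0.69, against 0.17-0.18 when the calendar does not change. At 0.39, a level ratio must reach exp(1.96×0.39) = 2.15 to be significant; at 0.18, exp(1.96×0.18) = 1.42.

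**Model 2.** When both series share the calendar, the difference terms (β6 + 3β7, and β7) give ratios of 0.98-1.04.

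**If 2024 was not in fact shifted but the model shifts it.** For full vaccination, the false level ratio is 0.90-1.13 as planned, and 1.13-1.67 with separate harmonics and the shift kept. For first doses it is 1.38-2.27 as planned and 1.29-1.89 with separate harmonics (amplitudes 0.5/0.3 and 1.0/0.5). Separate harmonics do not remove this error.

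**The case against.** The strongest reply is that the outcome may simply be the first dose. The Outcomes and Data analysis sections speak of receipt, and the Introduction quotes 2022 coverage as at least one dose. If first doses kept their calendar, nothing goes wrong in 2023. This stands, and it is why the point is conditional. The Sample size wording nevertheless points to completion, and the protocol does not settle the matter.

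A reader might infer that the schedule change manufactures a favourable campaign effect. The plan as written does not support that. With the 2024 shift correct, the level bias in these fits is downward, and simulated rejection was 0-7%, no higher than the 12-15% from the same simplified fits with an unchanged calendar. Upward figures appear when the six-month shift is left out or did not occur.

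A reader might also infer that the Model 1 versus Model 2 comparison would point to a co-intervention that never happened. The protocol uses that comparison to detect concurrent events as well, and a programme-wide schedule change is one. Flagging it would be correct. Model 2 is thus a real safeguard for the main comparison, but not for the subgroups or for the separate-series estimates.

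Finally, no monthly counts are given, so all sizes rest on assumed seasonality. This stands too. Another peak month, or an interruption one month later (49 rather than 48 baseline months), moves the figures and can turn a few of them slightly upward.

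**Conclusion.** The point holds in a conditional form. The seasonal pattern is fixed across a baseline in which the protocol itself places a change of schedule. Under the full-vaccination reading, and if the 2024 shift is right, the Model 1 level change is biased by roughly -2% to -16%, and its standard error is about two to four times what it need be. The main risk is a missed campaign effect, not a false one. The slope change is affected less predictably. Under the first-dose reading the bias is about 0 to -4%. The range illustrates the size under the stated shapes and is not a bound.

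It would go too far to say that the protocol has misdated the schedule change. The switch to one dose in 2023 and the change cited for the year after the interruption may be two separate events. The text does not say, and the passages must be reconciled.

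**What to change.** 1. State which dose counts as the event in 2020-2022, and use the same definition in the Outcomes, Sample size and Data analysis sections.
2. In Models 1 and 2, interact the four harmonic terms with an indicator for 2023 onward, so that 2020-2022 and 2023-2025 each have their own pattern. Apply any shift for the post-interruption year to the later pattern.
3. Before keeping the six-month shift, reconcile the date of the schedule change between the Introduction and the Data analysis section, name the calendar year meant, and check the shift against the actual school vaccination calendar. Step 2 without this check can make matters worse, because separate harmonics do not remove the false upward level change from a shift that did not occur.

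The cost is a few sentences and four more parameters. If the calendar did not change, generalised least squares with autocorrelation 0.3 puts the rise in standard error at 0.7-1.3% for the level change and 0.8-4.2% for the slope change.

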### Immunisation program impacts

In Australia, the prevalence of the HPV types in women aged 18 to 24 years old which were targeted by the vaccine declined significantly from 28.7% in the pre-vaccination era (2005-2007), to 2.3% in vaccinated women after vaccine introduction (2010-2012).
^
5
^ The rate of high-grade cervical disease has also declined dramatically, by 2014 it dropped to less than half the 2007 rate in women under 20 years of age.
^
5
^ The introduction of the Gardasil 9 vaccine is expected to prevent up to 90% of cervical cancers. Some research suggests that increased HPV vaccination, together with greater participation in screening, has the potential to eliminate cervical cancer in Australia and elsewhere within a few decades.
^
5,
6
^

In Australia, young Aboriginal and Torres Strait Islander (hereafter, respectfully, Aboriginal) people do not receive their HPV vaccine dose, resulting in missed opportunities to be protected from HPV-related cancers.
^
4
^ This is particularly important as rates of cervical cancer in Aboriginal women are twice those of non-Indigenous women, mortality rates more than three times higher, and screening participation rates lower.
^
6–
9
^ The recent change to one HPV dose will have substantive impact on meeting the recommended dose proposed by WHO.
^
4
^ In 2022, the Australian national rate of having at least one dose of HPV vaccination for young people turning 15 years old was 83.0% for Aboriginal females and 78.1% for Aboriginal males.
^
10
^ In Western Australia (WA), the completion rates were 81.4% of Aboriginal females and 78.6% of Aboriginal males. Despite these overall rates being reasonable, there are pockets of concern within Western Australian, including the capital of the State, Perth. In 2022, 51% of Aboriginal young people in Perth received one dose of HPV vaccine during Year 7 and this did not improve in 2023 (unpublished data).
^
11
^ Substantive resources are needed to improve these rates both in school catch-up programs and within the community. To eliminate cervical cancer, improving HPV vaccine rates amongst young Aboriginal people is necessary.

Despite the decline in HPV, there are a number of reported barriers associated with HPV vaccine uptake including adolescents’ lack of awareness and knowledge, not feeling informed, and parental concerns around sexual activity and vaccine safety.
^
12

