Based on the advice from DeeBlanche, we will use TikTok as our platform for young people and Instagram and Facebook for families. For young people, we will engage at least five Aboriginal TikTok ‘micro-Influencers’ who have been identified in stage 1. Micro-Influencers are defined as Influencers who have up to 10,000 followers, have high engagement rates, strong relationships with their followers, and their opinions and perceptions are highly valued amongst their followers. Based on the experience of our social media team, micro-Influencers are the most appropriate type of Influencers to deliver this campaign compared to other types of Influencers (e.g. mega- and macro-Influencers). With the support of our social media team, micro-Influencers will provide content in their style. We will prioritise Aboriginal micro-Influencers, and they will be paid based on their industry rates, and own their own content. They will be required to add in #sponsored or equivalent to their posts. Influencers will not be expected to respond to comments on their posts, however, posts will be monitored by the social media team to provide feedback and mitigate any negative publicity or misinformation. During this stage, we will also develop linktrees that will be used as part of the campaign and will direct young people to relevant health services for catch-up HPV vaccination. For families, we will deliver content targeted to them via Instagram and Facebook as this platform has more engagement with this slightly older demographic. The Instagram and Facebook content will be general advertisement information developed by our social media team based on interviews in stage 1.

*Aim 2b: Implement a social media campaign*

We will deliver the campaign in Year 2 of the project (
Figure 3). The campaign will start prior to school term 1 and continue on to term 3. The timing of the campaign is to coincide with the school vaccination program, including parent consent and HPV dose 1 and the HPV vaccine catch-up program.
Figure 2 provides a social media campaign journey and focuses on the ‘engage ➔ excite ➔ convert’ part of the digital marketing strategy.
**‘Engage’** is priming young people about the social campaign for HPV. This will include the release of our campaign brand and launch of the website (weeks 1-6).

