•Level change at the end of the social media campaign (i.e. three months post the beginning of the social media campaign).•Change in slope.

In addition to the above model, for both outcomes, we will also fit the following single model (Model 2) that incorporates both the intervention and control series:

$$\text{Model}\;2:\log Y_{t}=\beta_{0}+\beta_{1}t+\beta_{2}I+\beta_{3}\left(t-T_{I}\right)I+\beta_{4}G+\beta_{5}\mathrm{tG}+\beta_{6}\mathrm{IG}+\beta_{7}\left(t-T_{I}\right)\mathrm{IG}+\text{seasonal}+\text{offset}+\epsilon_{t}$$
where

$Y_{t},T_{I},I,t,\text{seasonal},\text{offset and}\;\epsilon_{t}\;$
are as described above.

G
 represents the series with a value of 1 representing the intervention series, and a value of 0 representing the control series.

$\beta_{0}$
,

$\beta_{1}$
,

$\beta_{2}$
 and

$\beta_{3}$
 are as described above for the control series.

$\beta_{4},\beta_{5},\beta_{6}\;\text{and}\;\beta_{7}$
 represent the interactions between time and the intervention series. Specifically,

$\beta_{4}$
 represents the difference in the intercept at the beginning of the series between the intervention and control series,

$\beta_{5}$
 represents the difference in slope between the intervention and control series in the first segment,

$\beta_{6}$
 represents the difference in the level change between the intervention and control series, and

$\beta_{7}$
 represents the difference in the change in slope between the intervention and the control series.

We will compare the estimates of level change at the end of the social media campaign and change in slope between Model 1 and Model 2. This comparison will allow us to assess the possibility of whether a co-intervention/concurrent event may explain our findings.
^
35
^

We will plot interrupted time series graphs for all outcomes and series using the recommendations of Turner et al.
^
43
^ These plots will include: data points, trend lines, seasonality estimation and confidence intervals surrounding the trend line and counterfactual estimates. Segments will clearly delineated by breaks in the trend lines.

Subgroup analysis

We will fit Model 1 for the primary and secondary outcomes for the intervention series separately by:
•Sex (Females, Males)•Location in Perth (North West, North East, Central, South West and South East)

Influencer data

All qualitative information will then be synthesised descriptively, key messages will be identified, with thematic analysis completed using Nvivo software.

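### The offset counts vaccinated youths as still exposed, so a lasting campaign effect can look like fading in the change in slope

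*Protocol article*

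**What the plan says.** For the primary outcome the Data analysis section states that "we will count the number of youths aged between 12 and before their 15"th birthday and have received the vaccine, month by month. The offset is defined there as follows: "The log of the relevant population (i.e. all Aboriginal youth aged between 12 and before their 15"th birthday, per month. Its stated purpose is that it "will be included as an exposure offset to adjust for any changes to the population over time". Vaccinated youths are not removed from it, and depletion of the unvaccinated pool is not mentioned. The two effect measures are the level change at the end of the campaign and "Change in slope". The same measures are taken from Model 2, which adds the control series.

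Three other statements bear on the point. The Introduction says the programme has been single-dose since 2023. The section on immunisation programme impacts says "In 2022, 51% of Aboriginal young people in Perth received one dose of HPV vaccine during Year 7". Stage 2 describes links that "will direct young people to relevant health services for catch-up HPV vaccination".

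**The concern.** Vaccination is counted here as a one-time event. About half of Perth's Aboriginal youth leave Year 7 unvaccinated, and catch-up doses come from that finite pool. If the campaign raises the chance that an unvaccinated youth is vaccinated, and keeps it raised, the pool shrinks, and the same chance then yields fewer doses each month. The planned offset follows births and migration but not this shrinkage, so a constant effect shows as a ratio that rises at launch and then drifts down. The drift enters beta3 in Model 1. It also enters beta7 in Model 2, since the campaign leaves the control pool untouched. What is at stake is that a lasting effect could be reported as a waning one.

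**Working it through.** The plan gives no figure for the slope, so there is none to reproduce. Its 85% power concerns a shift in average proportions and is not affected.

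**Inputs from the protocol article.**
- 89 youths per birth month (Sample size).
- 51% vaccinated in Year 7 in Perth, and 78.6% (males) and 81.4% (females) for Western Australia (Immunisation program impacts).
- Segments January 2020 to December 2023 (48 calendar months) and January 2024 to December 2025 (24 months).

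**Assumptions.**
- 80% covered by age 15, with 60% as an alternative because Perth is named as a pocket of concern.
- Steady state before launch.
- Year 7 doses spread evenly and unchanged by the campaign.
- Catch-up at a constant monthly hazard h over the 24 months from age 13 to under 15, multiplied by 1.5 or 2 from January 2024 to the end of 2025.

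**Baseline at 80%.**
- h = ln(0.49/0.20)/24 = 0.0373.
- School doses: 0.51 × 89 = 45.4 per month.
- Catch-up doses: 0.29 × 89 = 25.8 per month.
- Total: 71.2 per month.

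**Hazard × 1.5 at 80%.**
- First month, catch-up ratio: (1 − e^(−1.5h))/(1 − e^(−h)) = 1.49.
- First month, all-dose ratio: (45.4 + 1.486 × 25.8)/71.2 = 1.18.
- The unvaccinated catch-up pool falls from 704 to 592 by month 24.
- Month 24, catch-up ratio: 1.25.
- Month 24, all-dose ratio: (45.4 + 1.249 × 25.8)/71.2 = 1.09.

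**Baseline at 60%.** h = ln(0.49/0.40)/24 = 0.0085. Catch-up is only 0.09 × 89 = 8.0 of 53.4 doses per month.

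The level and slope terms of Model 1 were fitted by least squares to the noise-free log ratios under the planned offset:

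| Covered by 15 | Hazard × | All-dose ratio, first → last month | Slope change per year, all doses | Slope change per year, catch-up doses | Fitted all-dose ratio at end |
|---|---|---|---|---|---|
| 80% | 1.5 | 1.18 → 1.09 | -3.7% | -8.4% | 1.08 |
| 80% | 2 | 1.35 → 1.15 | -7.6% | -15.2% | 1.12 |
| 60% | 1.5 | 1.07 → 1.06 | -0.5% | -2.4% | 1.06 |
| 60% | 2 | 1.15 → 1.12 | -1.2% | -4.7% | 1.12 |

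With catch-up doses divided by the unvaccinated catch-up pool, the slope change is 0.0% in all four rows, which is the truth built into the model.

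**Other delivery patterns.**
- One constant hazard from age 12 to 15 (80% covered), all of it raised by 1.5: the slope is -0.0110 per month (× 0.88 per year) under the planned offset and 0.000 under the unvaccinated offset. The fitted ratio ends at 1.12.
- Yearly school sessions plus catch-up, eight scenarios: slopes under the planned offset run from -0.0055 to +0.0045 per month. Each is lower than under the unvaccinated offset, by 0.0014 to 0.0112. In one of the eight (Year 7 uptake raised to 60%, catch-up hazard unchanged) the fitted ratio ends just below 1, at 0.993.

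**Effects that stop.** These used 80% covered. The range for the unvaccinated offset reflects how many 12-year-olds are counted as unvaccinated.
- 1.5-fold hazard for 4 months: -5.9% per year planned, -6.5% to -6.8% with the unvaccinated offset.
- Doubled hazard for 8 months: -16.7% planned, -17.4% to -17.7% with the unvaccinated offset.

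**The case against.** The strongest reply is that doses per head of population is a legitimate public-health quantity: it measures net doses. The unvaccinated-pool rate answers a different question, using a denominator that the campaign itself changes and in which those left may be harder to reach. Choosing between them is partly a choice of estimand. That stands, and it is why the planned rate should stay.

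The bias is also modest against noise. At about 71 doses per month with autocorrelation 0.3, the standard error of the slope change is about 6% per year from Poisson variation alone, so -4% is below one standard error. That too stands. It limits the harm but does not remove the bias.

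The point also depends on reading the outcome as new vaccinations per month. The Outcomes and Sample size sections speak instead of recipients by the 15th birthday and of the number turning 15 each month ("we anticipate approximately 89 Aboriginal youth turning 15 years old each month in Perth over the study period"). For coverage in that birthday cohort, the whole cohort is the right denominator and no fading arises. The model as written is nevertheless a monthly flow: the count, the offset and the statement that "Seasonality will be accounted for by including two pairs of sine and cosine harmonics with periods of 12 and 6 months" all describe new doses.

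A reader might infer four stronger things that the documents do not support:
- **That the offset causes the steep negative slope after a short campaign.** It does not. The effect has ended, and the slope is negative under either offset.
- **That a catch-up push shared by both groups leaks into beta6 through the pool.** No control coverage is given. The same hazard ratio gives essentially the same relative rise in catch-up doses whatever the pool size, and the pool does not jump at launch, so changing the offset would not alter beta6 there.
- **That brought-forward doses cannot be told from a lasting effect.** Under the planned offset they show as a dip below baseline: catch-up doses fall to 0.805 of baseline after the 8-month doubling.
- **That success always makes the slope negative.** Some school-session scenarios give a slope near zero or slightly positive, though still biased down.

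**Conclusion.** The point holds in limited form. With a one-time event and a whole-population offset, a sustained campaign effect biases the change in slope downward, and Model 2 does not correct it. Under a constant 50% rise in catch-up hazard through 2025, with 51% vaccinated in Year 7, the all-dose artefact is about -4% per year at 80% covered by age 15 and about -0.5% at 60%. A doubled hazard gives about -8% and -1%. These sizes rest on assumed hazards, an assumed Perth coverage by age 15, and an effect that lasts beyond the campaign; the documents supply none of the three. In these scenarios the fitted ratio remains above 1. The planned offset is not wrong as a measure of net doses. The error would lie in reading its slope as the persistence of the effect. This is a cheap improvement, not a flaw that invalidates the analysis.

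**What to change.** 1. Keep the whole-population offset and describe the result as net doses per population.
2. Pre-specify a further analysis, in each series, with the log of the number of 12-to-under-15-year-olds still unvaccinated at the start of the month as offset (population minus cumulative recipients in the same birth months).
3. Report cumulative coverage by birth cohort up to the 15th birthday. This matches the outcome defined in the Outcomes section and makes brought-forward doses visible.
4. State that a negative change in slope will not be interpreted as waning unless these analyses agree.
5. State whether the primary outcome is monthly new vaccinations or coverage at the 15th birthday.

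The cost is mostly wording and a derived denominator, since vaccination timing and date of birth are already in the register request. There are three burdens. The extract must include doses given before 2020 to youths already in the age band at the start. Register counts must be aligned with population estimates. The rate among those still unvaccinated needs cautious reading, because they may be harder to reach.
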